# Can a combined screening/treatment programme prevent premature failure of renal transplants due to chronic rejection in patients with HLA antibodies: study protocol for the multicentre randomised controlled OuTSMART trial

**DOI:** 10.1186/1745-6215-15-30

**Published:** 2014-01-21

**Keywords:** Human leukocyte antigen antibodies, renal transplantation, premature allograft failure, chronic rejection, screening, tacrolimus, mycophenolate mofetil, clinical trial, randomised controlled trial, randomized controlled trial, KCTU, CTU, trials unit, diabetes, kidney, graft failure, biomarker, biomarker-led care, DSA, non-DSA, multicentre, immunosuppression, usual care, treatment as usual, standard care, blinded, unblinded, EME funded, NIHR, optimised, optimized, intention-to-treat, per protocol

## Abstract

**Background:**

Renal transplantation is the best treatment for kidney failure, in terms of length and quality of life and cost-effectiveness. However, most transplants fail after 10 to 12 years, consigning patients back onto dialysis. Damage by the immune system accounts for approximately 50% of failing transplants and it is possible to identify patients at risk by screening for the presence of antibodies against human leukocyte antigens. However, it is not clear how best to treat patients with antibodies. This trial will test a combined screening and treatment protocol in renal transplant recipients.

**Methods/Design:**

Recipients >1 year post-transplantation, aged 18 to 70 with an estimated glomerular filtration rate >30 mL/min will be randomly allocated to blinded or unblinded screening arms, before being screened for the presence of antibodies. In the unblinded arm, test results will be revealed. Those with antibodies will have biomarker-led care, consisting of a change in their anti-rejection drugs to prednisone, tacrolimus and mycophenolate mofetil. In the blinded arm, screening results will be double blinded and all recruits will remain on current therapy (standard care). In both arms, those without antibodies will be retested every 8 months for 3 years. The primary outcome is the 3-year kidney failure rate for the antibody-positive recruits, as measured by initiation of long-term dialysis or re-transplantation, predicted to be approximately 20% in the standard care group but <10% in biomarker-led care. The secondary outcomes include the rate of transplant dysfunction, incidence of infection, cancer and diabetes mellitus, an analysis of adherence with medication and a health economic analysis of the combined screening and treatment protocol. Blood samples will be collected and stored every 4 months and will form the basis of separately funded studies to identify new biomarkers associated with the outcomes.

**Discussion:**

We have evidence that the biomarker-led care regime will be effective at preventing graft dysfunction and expect this to feed through to graft survival. This trial will confirm the benefit of routine screening and lead to a greater understanding of how to keep kidney transplants working longer.

**Trial registration:**

Current Controlled Trials
ISRCTN46157828.

## Background

The problem addressed by this study is premature transplant failure – kidney transplants do not last for the natural lifespan of most recipients. Premature in this context refers to the lifespan of the recipient^a^. Current death-censored 10-year transplant survival rates vary between 59% and 70%, so 30% to 40% of patients have their transplant for <10 years
[1]. Since 2000, a consistent annual attrition rate of around 3% of kidney transplants
[2] means that approximately 700 patients return to dialysis each year in the United Kingdom. Although many of these patients are eligible for a second transplant, the legacy of the first often makes it harder to find a well-matched second kidney. In addition, second (and any subsequent) transplants have a shorter lifespan than the original transplant, so the problem of premature failure becomes amplified. Of the various reasons why transplanted kidneys fail, the single most common cause is immune-mediated injury
[3].

Two types of study have linked antibodies (Ab) against human leukocyte antigen (HLAs) to immune-mediated injury and premature graft failure. Case–control studies have compared patients who have lost grafts with those in whom grafts are still working, performing retrospective analysis of prospectively collected serum samples. For instance, Mizutani *et al*.
[4] studied 39 patients with failed grafts due to chronic rejection (CR) and 26 matched controls with functioning grafts. In the former group, 72% had immunoglobulin G (IgG) HLA Ab, compared to 46% of controls. Similar results were obtained from a different study of a separate population
[5]. The surprising thing from these studies was the high incidence of HLA Ab in patients with working grafts. There are several potential explanations for this. It is possible that factors relating to the HLA Ab (such as complement fixing ability) or factors in addition to the Ab, influence the progression of CR and thus the timing of eventual graft rejection. A second, related possibility, is that all patients with HLA Ab develop pathology, but it progresses at different rates, such that patients showing up in the control groups in these studies are deteriorating more slowly. Evidence for this comes from Mizutani *et al*.
[4], who showed that their CR group with HLA Ab showed progressive deterioration of renal function prior to graft failure. The same progressive deterioration was seen in the control group of patients with HLA Ab, whose grafts did not fail. These data illustrate that CR is a time-dependent process in which progressive graft dysfunction precedes graft failure. Moreover, the time from development of HLA Ab to graft failure is highly variable in different people.

Separate studies have reported the prospective follow-up of outcomes in those with HLA Ab. Terasaki and Ozawa
[6] studied 2,231 patients. In a group of 479 with HLA Ab, the 2-year graft failure rate was 15%, compared to 6.8% in the 1,753 with no HLA Ab. This trial noted that the patients who failed within 2 years had worse renal function on testing than those that did not, consistent with the fact that CR is a progressive and time-dependent process and those that fail are at the end of this process. In another study, the same group
[7] reported that the 4-year survival rate for 1,329 patients, all with functioning transplants, was 58% for those with HLA Ab (158 patients) vs 81% for those without (806).

Lachmann *et al*.
[8] performed the best study to date. The study was based at a single centre in Berlin and had 1,014 patients with stable kidney function (for the 6 months pre-recruitment) and were on average 6 years post-transplantation. Patients were tested for HLA Ab and prospectively followed for 5½ years. Grafts failed in 37% of the 302 who had HLA Ab, but in only 17% of the 712 patients who tested negative for HLA Ab. Moreover, in this latter group, a subgroup of 195 patients had a repeat test performed 2½ years into the study. Of these, 148 remained negative and only 6% of grafts failed in this group. In contrast, 47 had developed new HLA Ab since the beginning of the study and 21% of these suffered graft failure, confirming that the development of new HLA Ab in the negative group was predictive of future graft loss. Finally, this study identified a difference between the prognostic value of HLA Ab that were specific for the donor, known as donor-specific antibodies (DSA), which were found in 33% of HLA Ab + patients, and those that were not (non-DSA), found in 66%. Graft failure rates were 51% over 5.5 years in patients with DSA and 30% in patients with non-DSA. In a subgroup of patients who had transplant biopsies, 78% of those with failed grafts and HLA Ab + had changes consistent with CR. They concluded that grafts in patients with HLA Ab were more than three times likely to fail than those without, even when corrected for age, sex, year of transplant, estimated glomerular filtration rate (GFR) and number of previous kidney transplants. These findings have been corroborated by a second study from the Netherlands
[9], in which the risk of graft failure with HLA Ab was also shown to be independent of graft dysfunction and proteinuria.

Therefore, the literature indicates that HLA Ab are a prognostic biomarker and could be used as a screening test to identify patients at high risk of premature kidney transplant failure. All transplant units in the United Kingdom have the ability to detect HLA Ab, but routine systematic post-transplant screening of patients has not been generally adopted because it is not clear how best to treat patients once identified. Although there is a widespread view in the literature that HLA Ab cause CR, there is no evidence of this in humans. The chief investigator’s group has been investigating patients with CR for several years and has evidence that the activity of T and B cells is most strongly associated with progression of CR and that this subgroup benefits from enhanced immunosuppression (Shiu *et al.*, manuscript in preparation). This study will therefore test a combined screening and treatment protocol for HLA Ab in a randomised controlled trial.

## Methods/Design

### Trial objectives

#### Primary objective

The primary objective is the 3-year graft failure rate for patients testing positive for HLA Ab at baseline or within 3 years of randomisation who receive an optimised anti-rejection medication intervention with prednisone, tacrolimus (tac) and mycophenolate mofetil (MMF) (treatment), compared to a control group who test positive for HLA Ab at baseline or within 3 years post-randomisation who remain on their established immunotherapy and whose clinicians are not aware of their Ab status.

#### Secondary objectives

Determine the 3-year graft failure rate in patients randomised to unblinded HLA Ab screening, compared to a control group randomised to blinded HLA Ab screening.

Determine whether the treatment influences patient survival.

Determine whether the treatment influences the development of graft dysfunction as assessed by the presence of proteinuria (protein/creatinine ratio (PCR) > 50) or a change in the estimated glomerular filtration rate (eGFR).

Determine whether the treatment influences the rate of acute rejection for these groups.

Determine the adverse effect profiles of treatment in this group, in particular whether they are associated with increased risk of infection, malignancy or diabetes mellitus (DM).

Determine the cost-effectiveness of routine screening for HLA Ab and prolonging transplant survival using this screening and treatment protocol.

Determine the impact of biomarker screening and the treatment on the patients’ adherence to drug therapy and their perceptions of the risk to the health of the transplant.

Collect regular samples from patients enrolled in the HLA Ab + groups to enable an in-depth scientific analysis of the HLA Ab and cells of the immune and repair systems and to develop more sophisticated biomarkers for progression and/or responsiveness to therapy (to be funded separately, not as part of the efficacy and mechanism evaluation (EME) programme).

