### Secondary end points

The secondary clinical end points are:

• 3-year graft failure rates in all patients recruited to the trial

• Patient survival

• Rate of progression of graft dysfunction, as assessed by the change in the degree of proteinuria (PCR > 50) or the change in estimated GFR over 3 years

• Rate of biopsy-proven rejection over 3 years

• Rates of culture- or polymerase chain reaction-positive infection, biopsy-proven malignancy and DM

• Health economic analysis of outcomes

• Analysis of adherence and perceptions of risk for the biomarker-led care (BLC) groups

• The secondary scientific end points are:

• Changes in characteristics of HLA Ab and laboratory parameters of T and B cell phenotypes and responsiveness for the HLA Ab + groups

• Change in numbers and phenotype of circulating CD34+ cells for the HLA Ab + groups

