#### Secondary analysis

A similar procedure will be followed for secondary binary outcomes. We will use Cox proportional hazards regression to analyse survival outcomes. For continuous secondary outcomes we will use a two-sample *t*-test, transforming data where they are skewed.

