#### Inclusion criteria

• Sufficient grasp of English language to give written and witnessed informed consent to participate

• Renal transplant recipients >1 year post-transplantation, male or female

• Aged 18 to 70 years

• Estimated glomerular filtration rate (eGFR) ≥ 30, based on the four-variable Modification of Diet in Renal Disease (MDRD) approach

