#### First visit

Post consent, patients who have not been screened for HIV or hepatitis B/C within the last 5 years will undergo additional screening tests for these viruses. Female patients who report they may be pregnant will have a blood test for beta-Human Chorionic Gonadotrophin levels. Once eligibility criteria have been met, the following baseline data will be recorded at recruitment:

• Weight

• Blood pressure

• Sex

• Ethnicity

• Age

• Date of birth

• HLA type

• HLA type of donor kidney (if known)

• Any significant past medical history, including history of diabetes mellitus, cause of renal failure, details of previous transplants and cause of graft loss, evidence of sensitisation pre-transplantation (panel reactive antibody and antibody specificities if known)

• Medication including doses

• PCR of urine sample

All patients will then have blood taken for;

• Baseline clinical parameters: full blood count (minimum haemoglobin, white cell count, platelets); biochemical series (creatinine, Na^+^, K^+^, bicarbonate, calcium, C-reactive protein, lipid profile, glucose); MDRD eGFR on latest creatinine; current calcineurin inhibitor 12-hour trough levels (as appropriate); total immunoglobulin levels

• Scientific analyses: 50 to 60 mL blood for separation of peripheral blood mononuclear cells (PBMC) and 20 mL for serum storage

• Analysis of HLA Ab status (10 mL clotted blood), as described above, which will allow randomisation to proceed

All patients will be asked to complete questionnaires to assess attitudes to risk and adherence.

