### Procedures for assessing efficacy parameters

Graft failure is defined as the return to long-term dialysis or re-transplantation. This will be measured from the date of recruitment and will be reported for failure due to any cause. The date of restarting dialysis or re-transplantation will be recorded on the Case Report Form.

Deteriorating renal function will be determined by linear regression analysis of the serial MDRD eGFRs from the point of recruitment (like that used by Dudley *et al*.
[14]). Deterioration is defined as a negative slope. To be valid, the linear regression should yield an adjusted *r*^2^ ≥ 0.35 and have *P* ≤ 0.05 for the slope value. Stable renal function will be defined as serial MDRD eGFRs that are not significantly different from the horizontal baseline (that is, *P* > 0.05 on linear regression analysis). An improvement in renal function will be defined as a change in the slope so that it becomes positive. Serum creatinine levels and MDRD eGFR for the 12 months preceding recruitment and for the whole time patients are on the trial will be recorded on the CRF.

Proteinuria is defined by the PCR of a urine sample and is significant if >50. The PCR will be recorded on the CRF.

Acute rejection is defined by a combination of: (a) an acute rise in serum creatinine prompting a renal biopsy and (b) any pathology on the biopsy that meets the criteria for acute rejection, according to the latest BANFF criteria. The number of biopsies and the appropriate biopsy reports will be recorded on the CRF.

A full economic evaluation will adopt a National Health Service (NHS) perspective. The 3-year outcomes are the rates of: (1) graft failure, (2) patient survival, (3) graft dysfunction (see definition above), (4) acute rejection and (5) culture-positive infection, malignancy or diabetes, together with (6) EQ-5D, which is a patient-specific quality-adjusted life years (QALY) measurement. Cost-effectiveness will use (1) to (5) where (1) is the primary and the others are secondary outcomes. Cost-utility will be measured using (6) (the EQ-5D questionnaire). The net benefit per patient will be calculated by multiplying QALY by the assumed maximum willingness-to-pay for QALY (£20,000 per QALY) and subtracting the costs. The costs of all interventions will be obtained from Guy’s or estimated by identifying relevant categories of resource utilisation or measuring the volume of each category and multiplying by the average NHS resource costs

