In summary, this trial will identify a group of patients at high risk of premature transplant failure. Therapy will be optimised for these at-risk patients, many of whom will be identified before they have started to deteriorate clinically. As described above, the natural history of untreated CR is of progressive loss of function, usually at a predictable rate, leading eventually to complete loss of graft function. Depending on the initial creatinine level, the time to graft loss will be variable, but graft loss rarely occurs without this period of progressive loss of function. Lachmann *et al*.
[8] reported a constant rate of graft loss from the start of their study, so we expect that the rate of graft loss in our study will be constant in the standard care group. We predict that optimised immunotherapy will change the natural history of the condition, and lead to stabilisation of function in a significant proportion (50%) of those with HLA Ab. This will be visible in our analyses of the secondary end points. Hopefully the treatment will prevent the predicted graft loss in the first 3 years for this group and thus impact on the primary end point of the study.

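### The protocol describes the proteinuria outcome (PCR > 50) in three ways that do not agree, and two of them, read literally, let patients already above 50 at entry count as positive

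*Protocol article*

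**What the plan says.** The protocol article describes proteinuria as an outcome in three places.

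- Secondary objectives: whether treatment influences the "development of graft dysfunction as assessed by the presence of proteinuria (protein/creatinine ratio (PCR) > 50".
- Secondary end points, with a 3-year horizon: "Rate of progression of graft dysfunction, as assessed by the change in the degree of proteinuria (PCR > 50) or the change in estimated GFR".
- Procedures for assessing efficacy parameters: "Proteinuria is defined by the PCR of a urine sample and is significant if >50".

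No unit is given with the figure of 50 in any of them.

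The only renal limit at entry is "Estimated glomerular filtration rate (eGFR) ≥ 30, based on the four-variable Modification of Diet in Renal Disease (MDRD) approach". Neither the inclusion nor the exclusion criteria mention proteinuria. "PCR of urine sample" is listed in the baseline data under First visit, and again in the 4-monthly data under Subsequent visits.

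On analysis, the Secondary analysis section says "A similar procedure will be followed for secondary binary outcomes", which points back to the Z-test on proportions. The adjusted models under Exploratory moderator analysis are for stratification factors. The Trial design section gives these as antibody status, current immunosuppression and site, so baseline PCR is not one of them.

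**The concern.** Development, presence and change are three different quantities. A patient with PCR above 50 at entry has the state at time zero, cannot newly develop it, and can still get better or worse. One data set can therefore give three different treatment effects, depending on which section the analyst follows.

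The presence reading is the weakest match to the stated objective. With no PCR limit at entry, it can mix patients who became proteinuric with patients who already were. If the latter stay positive in both arms, they add the same amount to both proportions and shrink the difference.

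The outcome is also used elsewhere: the economic evaluation lists the rate of graft dysfunction among its 3-year outcomes and refers back to the definition. If the choice stays open, it could be made after results are seen.

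**Working it through.** **1. The three descriptions side by side**

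| Section | What is to be shown | How it is judged | Uses the baseline value? |
|---|---|---|---|
| Secondary objectives | Development | Presence of PCR > 50 | No |
| Secondary end points | Rate of progression | Change in degree, with PCR > 50 in brackets | Implied by *change*, but a fixed cut-off is not a change |
| Procedures for assessing efficacy parameters | Significant proteinuria | PCR > 50 | No |

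The efficacy section is more specific on eGFR: a regression slope, limits on adjusted r² and P, and separate definitions of deterioration, stability and improvement. Proteinuria has no counterpart to this.

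**2. Can patients enter above 50?** Nothing in the eligibility criteria prevents it. The Discussion says of the at-risk patients "many of whom will be identified before they have started to deteriorate clinically", that is, many but not all. The protocol gives no share with PCR > 50 at entry.

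**3. What counting them could cost.** The protocol states no rate, power or sample size for this outcome, so there is no figure to reproduce. What follows is an illustration.

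Inputs:
- n = 285 per arm, which is 139 + 146 from Sample size calculations (sized there for the primary end point).
- p = new PCR > 50 among patients at or below 50 at entry: 30% control, 16% treated (assumed).
- q = share above 50 at entry: 0% to 40% (assumed).
- s = share of those still above 50 at follow-up: 100% in both arms (assumed).

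Counting everyone, the proportion in an arm is P = q·s + (1 − q)·p. Power of the two-sided 5% Z-test is Φ{[|P₁ − P₂|√n − 1.96√(2P̄(1 − P̄))] / √[P₁(1 − P₁) + P₂(1 − P₂)]}, with P̄ the mean of P₁ and P₂. The restricted analysis uses p directly, with n(1 − q) patients per arm.

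Worked case, q = 20%: P₁ = 0.20 + 0.80 × 0.30 = 0.440 and P₂ = 0.20 + 0.80 × 0.16 = 0.328, a difference of 11.2 points. Power is Φ{(0.112 × √285 − 1.96 × 0.688)/0.683} = Φ(0.79) = 78.6%. Restricted, n = 228 and the difference is 14 points: Φ{(0.14 × √228 − 1.96 × 0.595)/0.587} = Φ(1.61) = 94.7%.

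| q | Difference, everyone counted | Power, everyone | Power, PCR ≤ 50 at entry (difference 14 points) |
|---|---|---|---|
| 0% | 14.0 points | 97.9% | 97.9% |
| 10% | 12.6 | 90.5% | 96.7% |
| 20% | 11.2 | 78.6% | 94.7% |
| 30% | 9.8 | 65.1% | 91.6% |
| 40% | 8.4 | 52.1% | 87.1% |

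Other assumed rates give the same direction. With 20% v 10% and q = 10%, 20%, 30%, power at 285 per arm is 71.8%, 53.5%, 39.8% counting everyone, against 88.9%, 85.1%, 80.1% restricted. At 417 per arm (40% of the 1,043 per arm for hypothesis 2) it is 86.7%, 69.8%, 54.0% against 97.1%, 95.3%, 92.5%.

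**4. When the loss disappears.** Let treatment also clear existing proteinuria, with s = 90% control and 70% treated, q = 20%, and p = 30% v 16% again. Then P₁ = 0.18 + 0.24 = 0.420 and P₂ = 0.14 + 0.128 = 0.268. The difference is 15.2 points and power at 285 per arm is 97.0%, against 94.7% restricted. Counting everyone then costs nothing.

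**The case against.** The strongest reply is that the listed end point is the change, a change uses baseline, baseline PCR is collected, and the rest belongs in an analysis plan that is not shown. Part of this stands. Handling of baseline and derivation of secondary variables are commonly settled there, and their absence here is not the point. But the sections do not merely lack detail; they name different outcomes, and the bracketed cut-off leaves unclear whether the change is in the PCR or in threshold status.

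Three stronger readings are tempting, and the protocol supports none of them.

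- *Patients above 50 at entry are counted as new cases.* No section says so. The wording permits it, and nothing says how they are handled.
- *One stray value above 50 at any 4-monthly visit makes an event.* The efficacy section says how proteinuria is measured and when it is significant. It gives no rule for turning serial values into an event, so a false-event rate would price a rule that is not there.
- *The Discussion relies on proteinuria to show the effect.* Its remark about secondary end points follows a sentence on stabilisation of function, and the efficacy section defines stable renal function by eGFR regression.

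It is also fair to object that the power figures rest on assumed rates, and that restricting to patients at or below 50 removes people in whom progression or improvement is informative. Both stand. They limit the claim about size and are a reason to offer continuous change as an alternative.

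**Conclusion.** The point holds as an inconsistency. The Secondary objectives, Secondary end points and efficacy definitions describe different proteinuria outcomes. With no PCR limit at entry, presence of PCR > 50 does not measure development.

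The consequence is a mislabelled quantity and a possible loss of sensitivity. Randomisation makes the share already above 50 similar between arms on average, so bias between arms is not the concern. The size is not known: in the illustration the loss runs from nothing at zero prevalence to 79% against 95% power at 20%, provided existing proteinuria persists equally in both arms. It can vanish if treatment resolves it. No power is claimed for this outcome, so no stated figure is wrong.

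This is minor: one component of one secondary end point. The primary end point is unaffected.

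**What to change.** Use one outcome in Secondary objectives, Secondary end points and Procedures for assessing efficacy parameters, tied to the PCR at time zero. Either would do:

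- New onset: PCR > 50 during follow-up among patients with PCR ≤ 50 at time zero, with patients above 50 at entry reported separately. This fits the *development* objective.
- Continuous change in PCR, adjusted for its baseline value. This fits the *change* wording of the end point and keeps every patient.

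For patients who become antibody-positive later, time zero is the positive test, as the Primary end points section already sets. State the PCR unit wherever 50 appears. A rule requiring a second value to confirm onset is optional.

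The cost is wording only, since PCR is already recorded at baseline and every 4 months. The one downside is that patients proteinuric at entry leave the new-onset version.
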